#### 2.5.5 Exercise Adherence

Exercise adherence is captured for the TARE and CARE groups by the following measures: 1) percentage and the number of prescribed sessions attended (out of 48 sessions); 2) average minutes of exercise/week (76). Participants are considered compliant if they attend ≥ 80% of the total prescribed number of exercise sessions and ≥ 80% of the total prescribed minutes/exercise sessions. Reasons for any missed sessions are documented throughout the study, and a make-up session can be scheduled as soon as possible with no more than three supervised sessions allowed per week. Participants have a two-week window post the 16-week intervention to make up for any missed sessions due to potential illness, family or work obligations, and COVID-19-related issues. Any sessions not completed within the 18-week period is not made up and counted as missed session.

#### 2.5.6 Other Measures and Covariates

Patients’ sociodemographic, medical, health behavioral characteristics are collected using a self-reported questionnaire consisting of questions including demographics, socioeconomic status, medical conditions, concurrent medications, cancer treatment history, smoking status, and alcohol consumption. Dietary intake is assessed using the Automated Self-administered 24-hour (ASA-24) dietary assessment tool (77). Dietary intake is recorded by the participants at home on three days (i.e., two weekdays and one weekend day). Physical activity participation outside of the given intervention is assessed using an accelerometer (*Actigraph, Pensacola, FL*) at each assessment timepoint and a booklet of physical activity logs to record any form of daily structured exercise including type, duration, and intensity on a weekly basis, which is returned at the time of data collection visits or can be mailed in every four weeks.

### 2.6 Follow-Up Assessments

After the 16-week intervention, participants in the TARE and CARE groups will return 4 and 8 months after the post-intervention assessments to repeat the outcome measure testing. Medical record abstraction will occur for 8 years thereafter to assess prognostic outcomes (i.e. OS, DFS, etc.). During the follow-up period, participants will be encouraged to exercise independently, without study team supervision/intervention.

### 2.7 Adverse Events

Each patient is evaluated for potential adverse events (e.g., lymphedema, pain, muscle soreness, nausea, etc.) throughout the study period, which includes each biopsy procedure and each exercise session. Participants are provided with a phone number to contact study staff to report potential intervention-related adverse events. Participants are assessed and graded according to the NCI Common Terminology Criteria for Adverse Events (CTCAE) V5 and documented by the study personnel at each exercise session. Staff will report on study progress and injuries during weekly meetings either in person, by phone, or through weekly email updates. All adverse events, both serious and non-serious, and deaths that are encountered from initiation of study intervention, throughout the study, and within 30 days of the last study intervention sessions, should be followed to their resolution, or until the principal investigator assesses them as stable or determines the event to be irreversible, or the participant is lost to follow-up.

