### 2.4 Exercise Intervention

The CARE and TARE groups receive a 4-month exercise intervention at an exercise facility located within the cancer center, and all exercise sessions are supervised one-on-one by a clinical exercise trainer. Both exercise programs consist of a total of 48 sessions, provided three times per week for 16 weeks for approximately 60 minutes per session. Heart rate (HR) is monitored throughout all training sessions using a Polar^®^ heart monitor (Lake Success, NY). Each session begins with a 5-minute warm-up of low-intensity AE and concludes with 5 minutes of the same 3-4 static stretches conducted by the AC group, which will target major muscle groups, each held for 30 seconds. One-repetition maximum (RM) and peak oxygen consumption (VO_2peak_) obtained during baseline testing are used to determine resistance load for each exercise and aerobic intensity, respectively. The details of a single exercise session of each CARE and TARE program are illustrated in **Figure 4**.

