#### 2.4.3 Attention-Control (AC)

Patients randomized to the AC group complete a 16-week home-based stretching program with the same stretches in the CARE and TARE groups at the end of their sessions. Minimal caloric expenditure is expected to be incurred as the stretches are low-intensity, low-impact, and low-volume. Participants are given an instructional booklet and trained in how to use the booklet to maximize the standardization of the home-based stretching (30) and increase compliance (31). Participants are also asked to complete weekly records detailing flexibility compliance and any physical activity performed outside of the study. At the end of the initial 16-week period, the AC group will be offered the 16-week CARE program weeks. Participants in the AC group who choose to perform the CARE program will complete one more assessment after the exercise program. Those who do not choose to partake in the CARE program will be finished with the study after the initial 16-week period.

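### Routine adverse-event grading is tied to exercise sessions that the attention-control arm does not have, so any adverse-event comparison with that arm would be open to ascertainment bias

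*Protocol article*

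**What the plan says.** Section 2.7 says that every patient is evaluated for adverse events "throughout the study period, which includes each biopsy procedure and each exercise session". Events are graded by CTCAE version 5 and "documented by the study personnel at each exercise session". A second route is open to everyone: "Participants are provided with a phone number to contact study staff to report potential intervention-related adverse events". Collection runs from the start of the intervention to "within 30 days of the last study intervention sessions".

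Section 2.4 describes the two exercise arms: "Both exercise programs consist of a total of 48 sessions, provided three times per week for 16 weeks", and "all exercise sessions are supervised one-on-one by a clinical exercise trainer".

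Section 2.4.3 describes the control arm: "Patients randomized to the AC group complete a 16-week home-based stretching program". These women are "asked to complete weekly records detailing flexibility compliance and any physical activity performed outside of the study". After week 16 they are offered the CARE programme.

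Section 2.5 schedules outcome assessments at baseline, mid-intervention and post-intervention. Section 2.5.1.1 makes the fat biopsy voluntary. Sections 2.8 and 2.9 name two between-arm comparisons, CARE versus TARE and CARE versus AC, for the primary and secondary outcomes. The article describes no between-arm analysis of adverse events.

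**The concern.** The one routine setting in which staff grade and record events, apart from optional biopsies, exists in two of the three arms. The examples given in Section 2.7 include soreness, pain and nausea. How often such complaints are recorded plausibly depends on how often someone asks. The phone route also requires an AC participant to decide first that her complaint might be due to the intervention, which for her is stretching. Participants, interventionists and outcome assessors all know the allocation (Section 2.3), so blinding gives no protection.

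AC is the trial's only reference for background symptoms after breast cancer treatment. A table of adverse events by arm invites comparison with it whether or not a test is planned. If events were found at different rates in the arms, that table would mix harm from exercise with intensity of enquiry. This cannot be repaired once data collection has ended.

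There is also a point about the period after week 16. AC women who take up CARE then have sessions, and so session-based grading. If events were tabulated by randomised arm over the whole study, those found during their CARE exposure would appear under AC.

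**Working it through.** **The plan's own figures.** The article gives no adverse-event rate and no safety calculation, so there is none to reproduce. The only figure borrowed here is the arm size in Section 2.8: 78 per group with 15% dropout gives 78 / 0.85 = 91.8, rounded up to 92, as stated.

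**Step 1: scheduled staff contacts in weeks 1 to 16** (Sections 2.4, 2.4.3 and 2.5).

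| Arm | Supervised sessions | Mid- and post-intervention visits | Total |
|---|---|---|---|
| CARE | 3 × 16 = 48 | 2 | 50 |
| TARE | 3 × 16 = 48 | 2 | 50 |
| AC | 0 | 2 | 2 |

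Optional biopsies come on top in every arm. Section 2.7 names sessions and biopsies as occasions for evaluating events. It does not name the two assessment visits, although they are contacts at which events could be elicited.

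**Step 2: direction.** More occasions for recording in CARE and TARE push towards more recorded events there. The two exercise arms have the same number of supervised sessions, so the comparison between them is not affected by this difference.

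**Step 3: what unequal capture could do (all inputs assumed).** Let the true risk p be equal in both arms, with capture 0.9 in an exercise arm and d in AC.

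- Recorded risks: 0.9p and dp. Apparent ratio: 0.9 / d, whatever p is.
- Chance of a nominally significant difference (two-sided 0.05, n = 92 per arm): Φ((Δ − 1.96·SE₀) / SE₁), where Δ is the difference in recorded risks, SE₀ is the pooled standard error and SE₁ the unpooled one.
- Example with p = 0.4, d = 0.5: recorded risks 0.36 and 0.20, so Δ = 0.16. SE₀ = √(2 × 0.28 × 0.72 / 92) = 0.0662. SE₁ = √((0.36 × 0.64 + 0.20 × 0.80) / 92) = 0.0651. (0.16 − 1.96 × 0.0662) / 0.0651 = 0.46, and Φ = 0.68.

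| Capture in AC (d) | Apparent ratio | p = 0.2: false difference; chance of p < 0.05 | p = 0.4: false difference; chance of p < 0.05 |
|---|---|---|---|
| 0.7 | 1.29 | 0.04; 11% | 0.08; 21% |
| 0.5 | 1.80 | 0.08; 35% | 0.16; 68% |
| 0.3 | 3.00 | 0.12; 71% | 0.24; 97% |

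With equal capture the ratio is 1 and the chance is 5%. The table shows how the result depends on the gap in capture; it does not estimate that gap.

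**Step 4: which events have another source.** Arm volume with a threshold of more than 10% difference (Section 2.5.3.5), the DASH questionnaire (Section 2.5.3.6) and the Brief Pain Inventory (Section 2.5.3.8) are outcome measures that do not depend on exercise sessions. The Figure 3 caption says that all groups are assessed unless noted. Read with Sections 2.4.3 and 2.6, the exceptions for AC concern the time after the 16 weeks. The figure itself is not shown, so the exact visits for each measure could not be checked. Muscle soreness, nausea, minor injury and short-lived events between visits have no such common measure.

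**The case against.** Four objections carry weight.

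- **No safety comparison with AC is planned.** This is correct. Sections 2.8 and 2.9 name comparisons for efficacy outcomes only, and TARE versus AC is not named for any outcome. A reader might infer that a planned safety analysis is biased; the article does not support that. The point concerns any comparison with AC that is made later.
- **AC is not without ascertainment.** Section 2.7 covers each patient, and its list of occasions is inclusive rather than exhaustive. AC women also attend the assessment visits and may volunteer for biopsy. Reading the contrast as 48 enquiries against none goes too far. Even so, the evaluation of each patient is a general intention, and the text attaches no scheduled enquiry for AC to it.
- **The trial would still inform on lymphedema and pain.** A reader might conclude that the trial can neither clear nor implicate exercise for these. That fails, because arm volume, the Brief Pain Inventory and DASH give AC a scheduled reference.
- **The full protocol may contain an event schedule by arm.** It may, and a condensed article need not print it. The point does not rest on that silence. It rests on what Section 2.7 states: where grading is documented, in a setting that AC lacks for 16 weeks.

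The concern about AC women's later CARE programme is conditional. It applies only if events are tabulated by randomised arm over the whole study, which the article does not say.

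**Conclusion.** The point holds in a limited form. As Section 2.7 is written, routine CTCAE grading happens at exercise sessions and optional biopsies. CARE and TARE have 48 sessions each in the randomised 16 weeks and AC has none. A comparison of adverse events with AC would be open to ascertainment bias towards more recorded events in the exercise arms, mainly for soreness, nausea, minor injury and events between visits. CARE versus TARE is not affected, and lymphedema, pain and upper-limb symptoms are less affected.

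The size is unknown. The ratios of 1.3 to 3.0 rest wholly on assumed capture probabilities, and the chances of a false finding also rest on assumed true risks. That the bias would occur is a likely consequence of the stated rule and is not shown by the document. The efficacy analyses and the sample size are untouched. The change is worth making because it is cheap and the information cannot be recovered afterwards.

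**What to change.** 1. Ask the same solicited adverse-event list, with the same recall period and grading, of all three arms at the existing mid- and post-intervention visits.
2. If a weekly item is added as well, put it on the physical activity log of Section 2.5.6 in all three arms, so that enquiry stays matched. Adding it for AC alone would create a new imbalance.
3. State that any comparison with AC uses only these common enquiries, within the randomised 16 weeks.
4. Report events captured at sessions separately, for CARE versus TARE.
5. Tabulate events during AC women's later CARE programme separately from AC.
6. Say how the 30-day window is to be read for women who have no supervised sessions.

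If the full protocol already has a matched enquiry for AC, it is enough to say so in Section 2.7 and apply items 3 to 6. The cost is one short form at two existing visits, a few minutes of staff time, and more minor events to process. No endpoint, sample size or treatment changes.

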### 2.8 Sample Size

We anticipate recruiting 276 patients over a 48-month period and randomizing 92 patients to each arm of the study. Our hypotheses and analyses regarding our primary and secondary outcomes will reflect the comparison between CARE vs. TARE, and CARE vs. AC. Since the primary analysis involves two statistical comparisons, we will apply Bonferroni adjustment to control the overall type I error rate at 0.05 level. We estimated samples sizes for these two comparisons with each evaluated at two-sided alpha = 0.025. Our estimates of exercise intervention effect sizes were derived from randomized clinical trials (78–80) in addition to our preliminary data (81); most significantly, a study comparison of traditional endurance training vs. high-intensity circuit training (80) with effect sizes for outcomes common to our proposed trial (fat mass, lean body mass) was approximately 0.5-0.6. Effect sizes comparing exercise interventions to AC groups were larger, on 0.7-1.0. Our preliminary data compared exercise to AC (15 subjects per group), effect sizes were on the order of 1.0 (body composition measures) to 2.5-3.0 (inflammatory and other biomarkers) (81). The sample size determination was based on the comparison of the primary outcome between the CARE and TARE group because we expected that the difference between the CARE and AC group was larger than that between the CARE and TARE groups. We used an effect size of 0.5, two-sided alpha=0.025, and 80% power to estimate the sample size for comparisons of CARE vs. TARE, yielding a required 78 participants per group. To account for an anticipated 15% dropout rate, we will randomly assign 92 participants to each of the three groups. This will provide 80% or higher power to detect effect sizes of 0.5 and higher for other outcomes. For the optional biopsies, the sample size has been estimated at 50 participants per group based on our preliminary work (81). This will provide 80% power to detect a between-group difference, at a two-sided 0.025 alpha level, when the effect size is 0.9 for biopsy outcomes.

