**Methods:**

The AIM trial is a prospective, three-armed, phase II randomized controlled trial investigating the effects of a 16-week supervised circuit aerobic and resistance exercise (CARE) program versus a traditional aerobic and resistance exercise (TARE) program and attention control (AC) on adipose tissue inflammation in breast cancer survivors. 276 patients who are diagnosed with stage 0-III breast cancer, post-treatment, sedentary, and centrally obese are randomized to one of the three groups. The CARE and TARE groups participate in thrice-weekly supervised exercise sessions for 16 weeks. The AC group are offered the CARE program after the intervention period. The primary endpoint is adipose tissue inflammation assessed by core biopsy and blood draw. The secondary and tertiary endpoints are sarcopenic obesity, physical fitness and function, and patient reported outcomes. The exploratory outcomes are long-term breast cancer outcomes.

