#### 2.5.1 Primary Outcomes

##### 2.5.1.1 Adipose Tissue Chronic Inflammation

M1 and M2 phenotypes are the primary outcomes. As the M1/M2 system alone does not accurately represent the heterogeneity of adipose tissue macrophages (ATMs) in obesity (32), we also examine secretion levels of inflammatory cytokines to provide a comprehensive examination of the presence of chronic adipose tissue inflammation, which include interleukin (IL)-6, IL-8, tumor necrosis factor-α (TNF-α), high-sensitive c-reactive protein (hs-CRP), leptin, and adiponectin. Participants can volunteer to undergo an abdominal subcutaneous fat biopsy under local anesthesia performed by a certified physician assistant ([name]) and are asked to refrain from foods for 12 hours and anti-inflammatory pharmaceuticals for 3-5 days prior to biopsy. Participants lie supine on the examining table while the biopsy site is prepped and draped in a sterile fashion. Under ultrasound guidance performed by a licensed technician, a local anesthetic is injected into subcutaneous abdominal fat (midway between the iliac crest and umbilicus) after which a small skin nick is made. The core biopsy device equipped with a 13-gauge needle is inserted at the incision site.

Approximately 4 samples are taken from a single site, roughly a total of 40mg to 120mg of fat tissue. The biopsy is taken at the Brigham and Women’s Hospital and transported to the Immune Assessment Laboratory at the Center for Immuno-Oncology for processing. One sample is flash-frozen in liquid nitrogen and stored until RNA isolation, and the rest of the tissue is digested with a collagenase solution to create a single-cell suspension. Appropriate batch testing is conducted by research staff blinded to randomization.

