##### 2.5.1.2 Systemic Inflammation

Fasting blood is taken from the antecubital vein by a trained phlebotomist following the biopsy procedure. For each sample, two 10 ml tubes are collected into EDTA and Serum tubes, along with one additional lavender topped tube (whole blood in EDTA). Samples are centrifuged and then aliquoted and stored at -80°C for future measures. Blood samples are then transported to the Brigham Research Assay Core for batch analyses for IL-6, IL-8, TNF-a, and hs-CRP. Other related systemic biomarkers such as leptin, adiponectin, insulin resistance, insulin-like growth factor (IGF)-1, IGF binding protein (IGFBP)-3, lipid profile, estradiol, sex hormone-binding globulin (SHBG), and free testosterone are also analyzed through commercially available blood testing kits.

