### 2.9 Statistical Analysis

Initial descriptive analyses will be used to evaluate baseline comparability among the three intervention groups, using ANOVA, or Kruskal-Wallis tests for continuous variables and chi-square tests for categorical variables. Unless otherwise specified, Statistical testing will be conducted at a two-sided 0.05 alpha level to determine statistical significance. For our primary and secondary outcomes, the variables used for the primary analysis will be the 2- and 4-month measurements of trial outcomes assessed during and at the end of the intervention period. Linear mixed-effects models will be used with the longitudinal data for the between-group comparisons, where two indicator variables for the treatment group (TARE, AC) relative to CARE, the baseline value of the outcome, and an indicator variable for measurement time (2-month/4-month) will be included as fixed-effects and subjects as random-effects in the models. With Bonferroni correction applied, the Wald test will be performed at 0.025 two-sided alpha level for each of the two comparisons regarding treatment effects (i.e., CARE vs. TARE, and CARE vs. AC); the between-group differences will be reported with corresponding 0.975 two-sided confidence intervals. Significant group differences will be followed by stratified analyses within measurement time (two and four months), and testing of group-time interactions, to evaluate treatment group differences within measurement time.

Post-intervention outcomes will be evaluated using the same linear mixed-effects models. The dependent variables will be the 8- and 12-month post-intervention measures, with the 4-month post-intervention measure, included as a fixed-effect.

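### The 0.05 overall error claim counts the two arm comparisons but not the two named primary outcomes, so at least four primary tests run at 0.025

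*Protocol article*

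**What the plan says.** All places are in the protocol article.

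- **2.8 Sample Size** counts the family as two: "Since the primary analysis involves two statistical comparisons, we will apply Bonferroni adjustment to control the overall type I error rate at 0.05 level". It goes on: "We estimated samples sizes for these two comparisons with each evaluated at two-sided alpha = 0.025". The section refers to the primary outcome in the singular and does not name it.
- **2.9 Statistical Analysis** carries this into the test, "the Wald test will be performed at 0.025 two-sided alpha level for each of the two comparisons regarding treatment effects", and into estimation: "the between-group differences will be reported with corresponding 0.975 two-sided confidence intervals". The mixed model includes the baseline value of the outcome, so it is fitted once per outcome.
- **2.5.1.1 Adipose Tissue Chronic Inflammation** uses the plural: "M1 and M2 phenotypes are the primary outcomes". It then adds six tissue markers (IL-6, IL-8, TNF-α, hs-CRP, leptin, adiponectin) with the words "we also examine secretion levels of inflammatory cytokines to provide a comprehensive examination of the presence of chronic adipose tissue inflammation".
- **2.5.1.2 Systemic Inflammation**, also under the Primary Outcomes heading, adds blood markers: "Blood samples are then transported to the Brigham Research Assay Core for batch analyses for IL-6, IL-8, TNF-a, and hs-CRP".
- **Abstract, Methods**: "The primary endpoint is adipose tissue inflammation assessed by core biopsy and blood draw".

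**The concern.** Halving alpha protects against having two comparisons on one outcome. With M1 and M2 both primary, the same 0.025 is spent twice per outcome, four times in all, and the stated overall 0.05 no longer follows from the stated procedure. It would hold if one primary variable were fixed, or if success required both outcomes. The article says neither.

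At stake is what a positive result means. A significant difference on only one of M1 and M2 could be reported as a primary finding with error controlled at 5% when the true rate is higher. The loose boundary between primary and supporting markers under 2.5.1 leaves room for that choice to be made after the data are seen.

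**Working it through.** **1. The plan's own sample size.** Inputs from 2.8: effect size 0.5, two-sided alpha 0.025, power 80%, dropout 15%. Normal approximation: n = 2(2.2414 + 0.8416)² / 0.5² = 76.04, rounded up to 77 per group. The two-sample t-test (noncentral t) needs 78, with power 0.804. Then 78 / 0.85 = 91.8, rounded up to 92, and 3 × 92 = 276. The plan's figures reproduce, for one outcome at 0.025 per comparison.

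**2. Error rate with one outcome.** Bound: 2 × 0.025 = 0.05. Simulation with the shared CARE arm: 0.046. The claim holds in this case.

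**3. Error rate with M1 and M2.** Four tests at 0.025 give a bound of 4 × 0.025 = 0.10. Four independent tests would give 1 − 0.975⁴ = 0.096. The table shows the simulated chance of at least one rejection when no arm differs: three equal arms sharing CARE, rejection when |z| > 2.2414. The article gives no correlation between M1 and M2, so that column is an assumption.

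| Assumed correlation of M1 and M2 | Chance of at least one false claim |
|---|---|
| 0 | 9.1% |
| 0.5 | 8.5% |
| 0.7 | 7.9% |
| 0.9 | 6.7% |
| −0.9 | 6.6% |
| −0.98 | 5.6% |

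The negative rows are included because the Discussion reports that in the pilot the M1 ratio fell while the M2 ratio rose. If the two are close to complementary shares, they act almost as one variable and the excess nearly disappears.

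**4. Wider family, conditional only.** If the six further tissue markers also counted as primary, there would be 8 × 2 = 16 tests. Simulated rate: 31.7%, 24.3% and 11.7% at assumed correlation 0, 0.5 and 0.9.

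**5. Price of covering four tests.** Plain Bonferroni uses 0.05 / 4 = 0.0125 per test.
- At 78 per group and effect 0.5, CARE vs TARE power is 0.72; 80% would need 91 per group.
- Holm over the four tests gives about 0.85 at 78 per group, assuming outcome correlation 0.5 and CARE vs AC effects of 0.7 to 1.0.
- M1 and M2 come only from the optional biopsies. At the plan's inputs for these (50 per group, effect 0.9), recomputed power is 0.986 at 0.025 and 0.973 at 0.0125.

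**6. Holm for two comparisons on a single outcome.** At 78 per group, effect 0.5 for CARE vs TARE and 0.7 to 1.0 for CARE vs AC, power for CARE vs TARE rises from 0.81 to 0.88 (normal scale), or 0.80 to 0.87 (t-based).

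**The case against.** The strongest reply has four parts.

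- **An outcome hierarchy is normally left to the analysis plan, and this is a condensed article for a phase II trial.** That is true of a missing hierarchy, which is not the point here. The article itself asserts overall control at 0.05, from a count that disagrees with its own list of primary outcomes. That clash stands on the article's text alone.
- **The inflation is small.** This stands in part. For the two outcomes actually named primary it is a few percentage points at most, and less than one point if M1 and M2 mirror each other almost perfectly. The pilot result shows mean changes in opposite directions; it does not give the correlation within participants.
- **A reader might infer that every marker under 2.5.1 is primary, and so quote error rates of 12% to 32% or more.** The section heading and the abstract's mention of a blood draw make that reading possible. But 2.5.1.1 separates M1 and M2 from markers introduced with "we also examine secretion levels of inflammatory cytokines to provide a comprehensive examination of the presence of chronic adipose tissue inflammation", which reads as supporting evidence. Nowhere does the article say that a win on any one marker makes the trial positive. These larger rates are conditional and should not be the headline.
- **A reader might also infer that choosing Bonferroni over Holm is an error that leaves CARE vs TARE underpowered.** It is not. Bonferroni is valid for two comparisons, it delivers the planned 80% at 78 per group, and it pairs each test with a matching 97.5% interval. At the plan's biopsy inputs, power is already about 0.99, so Holm would add almost nothing for M1 and M2.

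**Conclusion.** The point holds in a limited form. The claim of overall 0.05 control is correct for one primary outcome and incorrect for the two that 2.5.1.1 names. The actual rate is about 7% to 9% for assumed correlation 0.9 to 0, and about 5.6% to 6.6% for −0.98 to −0.9. This rests on two assumptions: that a significant result on either M1 or M2 would count as a primary finding, which the article neither states nor excludes, and the correlation, which it does not give. Whether the remaining markers belong to the primary family is ambiguous and should be settled in the text. This should be fixed, but it does not undermine the design or the sample size calculation for a single outcome.

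**What to change.** Make 2.5.1, 2.8 and 2.9 agree, and align the abstract, by choosing one of these before outcome data are compared between arms:

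1. **One primary variable.** Name it, apply the two comparisons to it at 0.025 each, and label the other tissue and blood markers secondary or supportive. Cost: some markers lose primary status.
2. **M1 and M2 both primary, four tests adjusted.** For example Holm, with ordered p-values against 0.0125, 0.0167, 0.025 and 0.05. A two-step 0.025 / 0.05 rule applied separately to each outcome would not be enough. Cost: at the plan's biopsy inputs even plain Bonferroni at 0.0125 keeps power at 0.97. At effect 0.5 and 78 per group the loss is real (0.80 to 0.72 with plain Bonferroni), and Holm recovers it under the assumptions in step 5. Interval reporting must be restated: 97.5% intervals would not match, while plain Bonferroni at 0.0125 would pair with 98.75% intervals.
3. **Both must be significant.** State that a comparison succeeds only if M1 and M2 both reach 0.025. The error is then at most 2 × 0.025 = 0.05. Cost: joint power is below that of either test. At the plan's biopsy inputs it is still at least 1 − 2 × (1 − 0.986) = 0.972 per comparison.

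Optional with route 1: replace Bonferroni by Holm for the two comparisons, with the smaller p-value against 0.025 and, if that is significant, the other against 0.05. This keeps control at 0.05 and raises CARE vs TARE power from about 0.81 to 0.87–0.88 at 78 per group and effect 0.5. The downside is that the 97.5% intervals will not match every Holm decision, so 2.9 would have to say so.

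Every route is a change of wording and needs no additional participants under the plan's biopsy assumptions.
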